Despite the limited number of studies analyzing PAEE related to ACS, a significant gap remains in accurately assessing PAEE during free-living behaviors. Indirect calorimetry is widely recognized as the gold standard for measuring PAEE, as it directly quantifies oxygen consumption and carbon dioxide production, providing continuous, real-time data that capture the complex metabolic responses during activity (26). This direct measurement offers a significant advantage over methods that rely on predictive equations or self-reported data, which often oversimplify the dynamic and context-specific nature of free-living behaviors (26). Previous studies have frequently relied on stationary or semi-portable indirect calorimetry systems that are not well-suited for field applications (27). Although portable metabolic systems have been developed to facilitate outdoor assessments, their high cost and operational complexity limit their widespread use in educational and field contexts (27). As an alternative, researchers have employed established equations, such as those proposed by Riebe et al. (28) and Pandolf et al. (29). However, these equations were derived under highly controlled laboratory conditions (e.g., typically on treadmills) and, consequently, do not account for the variability of environmental factors (e.g., changes in speed, terrain, and weather), which critically influence PAEE in real-life settings, particularly in ACS (30). Another common practice for analyzing PAEE related to ACS has been through estimates based on counts measured by accelerometers (20, 31). However, accelerometers may not be the most appropriate devices for measuring PAEE in the context of ACS (32). Moreover, a recent study compared the PAEE associated with walking to that of using an e-scooter (33). However, this study was conducted under laboratory conditions, making it impossible to account for environmental factors that could influence PAEE. It is well known that the availability of safe and accessible routes directly correlates with increased PA among adolescents, which could, in turn, lead to higher PAEE (34). Additionally, PA levels may depend on adolescents’ perceptions in their commuting environment, considering factors such as fear of accidents, infrastructure, and social norms related to active commuting behaviors (35). Therefore, it is crucial to compare the PAEE associated with different modes of commuting to school in free-living conditions. Furthermore, developing a context-specific equation that incorporates key commuting characteristics (e.g., speed and distance) would provide a more accurate estimation of PAEE associated with this behavior.

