Therefore, this protocol describes the rationale and methodology of the ENERGY expenditure of school Commuting study (The ENERGYCO study). ENERGYCO project will address the gaps and limitations in the existing scientific literature regarding the PAEE that occurs during cycling to school. Considering the previous literature and existing gaps, the ENERGYCO project will be divided into two phases. Phase I will focus on using a portable metabolic system to assess PAEE associated with different modes of commuting (i.e., walking, cycling, motorized vehicles) under free-living conditions in Spanish adolescents. Additionally, Phase I will serve to develop a predictive equation that will be used in Phase II to measure PAEE associated with different modes of commuting to and from school. Additionally, considering the ongoing debate regarding the health benefits of ACS and the scarcity of studies examining the effects of school-based cycling interventions on RMR and PAEE, the Phase II will aim to assess the effects of a school-based cycling intervention on RMR and PAEE, as well as on other physiological (i.e., basal heart rate, blood pressure, and body temperature), physical (i.e., PA levels, anthropometric measures, body composition, physical fitness, and motor competence), and psychosocial outcomes (e.g., perceived barriers to active commute to school, self-esteem, and mental health) on Spanish adolescents. It is hypothesized that, in Phase I, using a portable metabolic system under free-living conditions will provide accurate and distinct measurements of PAEE associated with different commuting modes in Spanish adolescents. Specifically, we hypothesize that these measurements will highlight significant differences in PAEE across commuting modes, offering a more precise understanding of how commuting impacts adolescents’ physical activity levels. Additionally, we expect the data collected in Phase I to contribute to the development of a valid and reliable predictive equation for estimating PAEE during commuting to and from school. we hypothesize that a school-based cycling intervention will lead to a significant increase in both RMR and PAEE compared to a control group. We further hypothesize that the intervention will improve physiological outcomes (e.g., reductions in basal heart rate), physical outcomes (e.g., enhanced physical fitness and motor competence), and psychosocial outcomes (e.g., increased self-esteem) among Spanish adolescents.

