### Study population

2.2

In the Phase I of the ENERGYCO study, a convenience sample of 50 students (12–16 years old) will be recruited to assess the PAEE of different modes of commuting to school (i.e., walking, cycling, and motorized-vehicle). For Phase II, the ENERGYCO study will recruit a random sample of students (*n* = 300) from the three Spanish cities (i.e., Granada, Almería, and Jaén). The intervention aims to assess the effects of a school-based cycling intervention in the RMR and PAEE related to cycling to school, as well as its impact on others physiological, physical, emotional, and psychosocial outcomes in Spanish adolescents. The randomization process is presented in Figure 1.

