
**Table 1 tab1:** Schools’ inclusion and exclusion criteria.

Inclusion criteria	Exclusion criteria
The school has a specific space for parking bicycles and allows their parking	The school does not have specific infrastructure to park or store bicycles
The school has at least two classes per grade	The school offers bus transportation to the adolescents
At least eight students from the school will agree to participate in the study	The school is already participating in other interventions focused on promoting healthy behaviors
Schools from urban areas	The school has implemented an intervention to encourage commuting to school within the last year
	Schools from rural areas

**Table 2 tab2:** Participants’ inclusion and exclusion criteria.

Inclusion criteria	Exclusion criteria
Adolescents’ females and males aged from 12 to 17 years old (both ages included)	Adolescents younger than 12 years or older than 17 years
Healthy participants who can ride a bicycle safely and without difficulty.	Participants with any injury or medical condition that prevents safe participation in cycling to and from school
Be able to cycle to and from school at least 3 days per week during eight consecutive weeks (Intervention group)	Insufficient ability to ride a bicycle or inability to cycle to and from school at least 3 days a week (Intervention group)
Not to cycle to and from school more than 3 days a week during the last year	Participants who have cycled to and from school more than 3 days a week during the past year
To present a valid signed consent from their parents or legal guardians	Participants without a valid, signed parental or guardian consent form
To present valid data at baseline and follow-up from all the outcomes assessed	Participants who do not provide valid data for all assessed outcomes at baseline and follow-up

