### Description and rationale of the ENERGYCO study

2.5

In Phase I the PAEE of different modes of commuting will be quantified by analyzing each participant individually in different controlled environments. For phase II, after recruiting schools and participants, an eight-week school-based cycling intervention will be implemented. The choice of an eight-week duration was based on the results reported in the systematic review by Dorothea et al. (47) on the effects of cycling interventions in a school setting. For example, although interventions lasting longer than 8 weeks demonstrate positive changes in physical fitness (43, 48), they also exhibit lower adherence, with a higher dropout rate among participants post-intervention. Therefore, considering that interventions lasting 4 to 8 weeks show effects on self-efficacy (49) or PA levels (50) and report a lower dropout rate, an eight-week duration was chosen for the school-based cycling intervention. The intervention will consist of adolescents having to cycle to and school for eight consecutive weeks. To encourage participants to complete the intervention, they will take part in a *Bikeability* training and different encouragement strategies will also be used during this period. Moreover, the ENERGYCO school-based cycling intervention shows relevant factors described in the current National Education Law for the curriculum of Compulsory Secondary Education. This approach is based on strategies proposed by the Active Living by Design Community Action Model (51), which involves preparing through the development of interventions, promoting education, and motivating students to cycle anywhere, as well as organizing activities with incentives and programs to engage participants. Regarding the control groups, participants in these schools will be asked to continue their daily habits. In addition, at the end of the eight-week cycling intervention in schools, control schools will be given the opportunity to conduct the *Bikeability* sessions and will receive all the motivational strategies used for the participating adolescents.

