#### Study assessment protocol

2.6.1

In Phase I, participants will perform three different simulations (i.e., commute by motorized-vehicle, walking, and cycling [see Figure 2]): (1) a simulation of driving to school will be performed by motorized-vehicle. After all the calibration process of the Cosmed K5 (both, flow and gas analyzers will be calibrated before every gas exchange measurement), a face-mask attached to the K5 will be place and gas exchange will be check during a two-minute period before the measurement start. After the check phase, gas exchange recording start during a five-minute period, while participants remain seated. Then, the participants will simulate commute in a motorized-vehicle by remaining seated in a chair for another 15-minute period, having previously walked for 2 mins simulating that participants are moving toward the motorized-vehicle from home. After this first simulation, there will be a five-minute period of cooling down. The total time of this first test will be 27 min. (2) A simulation walking to school will be conducted in a closed circuit defined by the research staff. The same procedures mentioned before will be followed. Then, the participant will walk for 15 min (the participant will determine the speed and intensity of walking) and finish with a five-minute cool down; (3) Participants will simulate a cycling route. They will wait for five-minute after walking and they will start cycling during 15-minute period along the designated route. The simulation will finish with a five-minute cool down period. The total time used in the walking and cycling simulations will be 45 min. These times were chosen because an average walking speed of 4.4–4.6 km/h would not exceed the distance Spanish adolescents are willing to walk to their educational center (1,350 m) (52). While no study in Spanish adolescents indicates the distance, they are willing to cycle to school, we estimated a distance of 4,200 m, the threshold distance used for Australian adolescents (53), with which a speed of approximately 15 km/h would not exceed 15 min. Detailed visual information on the evaluation and calibration process of the Cosmed K5 (Cosmed, Rome, Italy) can be found at the following link.^1^ In order that one active mode of commuting (e.g., walking) does not affect the post exercise oxygen consumption, thus PAEE, of the subsequent active mode of commuting (e.g., cycling), participants will alternate randomly by first performing the simulation of walking or cycling. In addition, the alternation of starting on the bike and walking will be counterbalanced by having the same number of participants starting on the bike or walking. Finally, all data will be downloaded using PC OMNIA.9 software v3.30.79 (Cosmed, Rome, Italy).

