Furthermore, studies focus on assessing the PAEE related to ACS in free living conditions have used accelerometer counts (20, 97) or heart rate (12) instead of indirect calorimetry. Indeed, as far as we know, two studies focus on young population used indirect calorimetry to measure the PAEE associated to different routine activities (98) or just walking in a treadmill (99), but both of them were carried out under laboratory conditions. The study by Schuna et al. (98) involved 106 American children and adolescents (6 to 18 years old) who completed a series of activities such as sitting, watching movies, coloring, climbing stairs, playing basketball, or jumping. Authors concluded that the lowest average PAEE values were associated with sitting and watching movies, while jumping was the activity that caused the highest average PAEE. While the study by Tudor-Locke et al. (99) evaluated the cadence produced by different walking speeds (an indirect measure of intensity) in young people aged 6 to 20 in a controlled trial. Participants completed multiple 5-min series on a treadmill, ranging from 0.80 km/h to 8.04 km/h. Steps were counted visually, and intensity was objectively measured using a portable metabolic system. Therefore, the ENERGYCO study will contribute to advancing knowledge on PAEE associated with different modes of commuting to school. To our knowledge, this will be the first study to objectively measure PAEE in adolescent commuters using indirect calorimetry in free-living conditions.

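### Phase I is described as free-living measurement but uses simulated commutes, so its equation's validity on real Phase II trips and at age 17 is not shown

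*Protocol article*

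**What the plan says.** **The claim.** The Introduction sets the Phase I aim as PAEE for walking, cycling and "motorized vehicles) under free-living conditions in Spanish adolescents", and the hypothesis that follows uses the same setting. The Discussion contrasts the study with earlier laboratory work and concludes that, to the team's knowledge, "this will be the first study to objectively measure PAEE in adolescent commuters using indirect calorimetry in free-living conditions".

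**The procedure.** Section 2.5 says that PAEE will be "quantified by analyzing each participant individually in different controlled environments". In section 2.6.1 the walking simulation "will be conducted in a closed circuit defined by the research staff". Cycling follows a designated route for 15 minutes. For the vehicle, after a 2-minute walk, "the participants will simulate commute in a motorized-vehicle by remaining seated in a chair" for 15 minutes. The Figure 2 caption also calls all three controlled simulations.

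**The use.** Section 2.7.1.2 takes PAEE for Phase II cycling trips from equations developed in Phase I, with distance, speed and heart rate among the predictors, cross-validated against Cosmed K5 values. PAEE is one of the two primary outcomes.

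**The ages.** For Phase I, "a convenience sample of 50 students (12–16 years old) will be recruited" (section 2.2). Table 2 admits participants "aged from 12 to 17 years old (both ages included").

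**The concern.** The article gives Phase I a property that its procedure lacks. Both statements are printed in the current text, so condensing a longer protocol does not explain the difference, and the limitations in the Discussion do not mention it.

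The article's own reasoning makes this more than a matter of wording. The Introduction sets aside existing equations because, having been derived under tightly controlled laboratory conditions, they "do not account for the variability of environmental factors (e.g., changes in speed, terrain, and weather"), and it faults a recent e-scooter study for being done in the laboratory. An equation derived from simulated commutes and applied to street trips is open to a milder form of the same criticism.

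Two things are at stake: a novelty claim that goes beyond what is measured, and a primary outcome in Phase II whose accuracy on real trips, and in the oldest participants, would be taken for granted.

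**Working it through.** The plan gives no statistical figure to reproduce on this point. The check compares passages, with some simple arithmetic on times and ages.

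**1. Is any real commute measured in Phase I?** The stated session times (section 2.6.1) are filled by the simulation segments:
- Vehicle: 5 min seated recording + 2 min walk + 15 min in the chair + 5 min cool-down = 27 min, as stated.
- Walking and cycling: 15 + 5 + 5 + 15 + 5 = 45 min, as stated.

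No segment is a home-school trip. Section 2.4.1 adds that Phase I runs outside the school timetable and without contact with schools. The free-living description therefore does not fit the procedure.

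**2. Which part of the procedure feeds Phase II?** The closed circuit is stated for walking only and the chair for the vehicle only. The Phase II outcome definition in section 2.7.1.2 applies the equations to cycling, so the relevant Phase I data are the rides on the designated route. The article does not say whether that route has slopes or stops.

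**3. What range do the Phase I rides cover?** Each is described as a 15-minute period. At the 15 km/h assumed in section 2.6.1, that is 15 × 0.25 = 3.75 km. The distance the plan has in mind, 4,200 m, takes 4.2 / 15 × 60 = 16.8 min at that speed, not at most 15 min as the section says; covering it in 15 min needs 4.2 / 0.25 = 16.8 km/h. A real trip of the plan's own reference distance at the plan's own speed would thus outlast the Phase I ride.

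**4. Does the planned validation cover real trips?** Section 2.7.1.2 describes K5 measurement in Phase I and equations in Phase II. Read that way, the cross-validation uses simulated rides and tests the fit within them. Table 3, however, marks the K5 for energy expenditure in both phases. No K5 procedure on Phase II trips is described, so the article leaves the source of the validation data unclear.

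**5. Ages.** Phase I covers 12, 13, 14, 15 and 16: five year-ages. Table 2 covers 12 to 17: six. One of six, age 17, lies outside the derivation range. This is a count of year-ages, not a share of participants; the article gives no expected age distribution.

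**The case against.** The strongest reply is that Phase I is far from a treadmill study. Walking pace is self-chosen (section 2.6.1), GPS records distance, speed and duration (Table 3), and outdoor temperature is logged (section 2.7.2.19), so speed and weather can vary. Heart rate is in the equation and is recorded on each Phase II cycling trip (section 2.7.2.2), so it carries part of the effect of a gradient or a stop. Section 2.7.2.18 measures terrain slope, plans to use it as a confounder, and adds a second PAEE estimate from GPS with accelerometry. Only 17-year-olds are extrapolated, and age is not among the predictors named. All of this stands, and it limits the point.

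A reader might go further and infer that the equation has no support in Phase II, or that it is the only source of PAEE there. The documents support neither reading, because of heart rate, the planned use of slope, the GPS-accelerometry estimate and the K5 entry in Table 3.

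A reader might also try to size the error from cycling mechanics. Take assumed values: 60 kg rider, 12 kg bicycle, 15 km/h (4.17 m/s), rolling coefficient 0.006, drag area 0.5 m², air density 1.2 kg/m³.
- Level: (72 × 9.81 × 0.006 + 0.5 × 1.2 × 0.5 × 4.17²) × 4.17 ≈ 39 W.
- Added by a 2% gradient: 72 × 9.81 × 0.02 × 4.17 ≈ 59 W.
- Ratio: (39 + 59) / 39 ≈ 2.5.

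That ratio is mechanical power at a fixed speed. It ignores heart rate in the equation, riders slowing uphill and the return trip, so it is not an estimate of error in PAEE.

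Nor should a reader conclude that the course must be rebuilt with slopes and stops: the article does not say that the designated route lacks them.

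The reply does not remove the contradiction over the setting, nor does it show that the equation is accurate on real trips.

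**Conclusion.** The point holds in a limited form. The free-living description in the Introduction and Discussion contradicts sections 2.5 and 2.6.1 and the Figure 2 caption, and should be corrected. The transport of the Phase I equation to real cycling trips and to age 17 is not shown, which is weaker than saying that it fails.

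The age gap is one of six year-ages. The size of any error on real trips cannot be derived from the article. Resting metabolic rate, the other primary outcome, does not depend on this equation. The Conclusion in section 4 speaks of instruments used outside the laboratory, which is accurate and needs no change.

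The verdict on transport assumes that the K5 is used in Phase I only, as section 2.7.1.2 describes. If it is also used on Phase II trips, as Table 3 suggests, and those data enter the validation, much of the concern about real trips would be met.

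**What to change.** 1. In the Introduction (Phase I aim and hypothesis) and the Discussion, replace the free-living description of Phase I with simulated commuting outside the laboratory, and withdraw the claim to be first in free-living conditions.
2. Recruit Phase I at ages 12 to 17 to match Table 2, or state that 17-year-olds are extrapolated.
3. Record the slope of the Phase I cycling route and, if it varies, consider slope as a predictor, since it is already measured in Phase II. Flag Phase II trips whose speed, slope or duration lies outside the Phase I range, and repeat the PAEE analysis without them. Because every Phase I ride is described as 15 minutes, a workable rule for duration is to flag trips that last longer; shorter ones fall within the recorded period.
4. Reconcile section 2.7.1.2 with Table 3: say whether the K5 is used on Phase II trips and, if so, whether those data validate the equation.

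The cost is wording, one more year in the Phase I age limit or a sentence declaring the extrapolation, and one extra sensitivity analysis. The downside is a more modest novelty claim.

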## Conclusion

4

The ENERGYCO study is designed to advance the understanding of cycling to school and its potential impact on physiological variables through an innovative two-phase structure. Phase I aims to quantify the energy demands of different commuting modes using out-of-laboratory gas exchange instruments, providing objective data on the physiological cost of cycling to school. The results from Phase I may offer valuable insights for schools, families, and practitioners, informing strategies to address sedentary behaviors and promote sustainable ACS, such as walking and cycling to school. Phase II will implement an eight-week school-based cycling intervention targeting Spanish adolescents. This phase will assess its potential impact on a range of outcomes, including physiological, physical, psychosocial, and emotional dimensions. By providing objective data on the short-term physiological effects of cycling to school, the ENERGYCO study aims to contribute to the evidence base supporting ACS strategies for adolescents. These results may help inform effective policies and practices, offering guidance to teachers, families, policymakers, and the clinical sector in implementing scalable and sustainable ACS-focused interventions. Finally, the ENERGYCO study aspires to contribute meaningfully to adolescent health and well-being, encouraging healthier and more active communities.
